## Abstract

**Background:**

Tobacco use disorder (TUD) remains a leading cause of preventable morbidity and mortality worldwide. Although nicotine replacement therapy (NRT) is recommended as a first-line treatment, its effectiveness is limited by persistent craving and withdrawal symptoms, resulting in high relapse rates. Acupuncture has been investigated as an adjunctive therapy; however, existing evidence is inconsistent and limited by methodological heterogeneity. High-quality pragmatic randomized controlled trials are needed. The co-primary outcomes are nicotine craving reduction (VAS) and biochemically verified 7-day point prevalence abstinence (PPA).

**Methods:**

This is a single-center, pragmatic, randomized, parallel-group controlled trial. A total of 220 participants with TUD will be randomly assigned (1,1) to receive either harmonizing mind acupuncture (HMA) plus NRT or NRT alone. The intervention period will last 6 weeks, with follow-up to 24 weeks. The co-primary outcomes are: (1) the change in nicotine craving measured by a visual analog scale (VAS) from baseline to week 6; and (2) 7-day point prevalence abstinence (PPA) biochemically verified by exhaled carbon monoxide at week 6. Secondary outcomes include exhaled carbon monoxide (as a continuous measure), quality of life, sleep quality, depressive symptoms, anxiety symptoms, and safety outcomes. Analyses will be conducted according to the intention-to-treat principle.

**Discussion:**

This pragmatic randomized controlled trial will evaluate the effectiveness and safety of HMA as an adjunct to NRT under real-world clinical conditions and provide clinically relevant evidence to inform integrative treatment strategies for TUD.

**Ethics approval and consent to participate:**

Ethical approval has been obtained from the Ethics Committee of the Affiliated Hospital of Yunnan University (Approval No.: KJR#20251111-R1-055). The study will be conducted in accordance with the Declaration of Helsinki. Written informed consent will be obtained from all participants prior to enrollment.

**Clinical trial registration:**

This trial has been registered with the International Traditional Medicine Clinical Trial Registry (ITMCTR) under registration number: ITMCTR2026000683 (https://itmctr.ccebtcm.org.cn/).

## Introduction

1

Tobacco use disorder (TUD) represents a substantial global public health burden and is responsible for more than 8 million premature deaths annually, according to the World Health Organization (1). It is a major risk factor for cardiovascular disease, respiratory disorders, and multiple types of cancer. Despite extensive tobacco control policies and public health interventions, achieving sustained smoking abstinence remains challenging. The strong addictive properties of nicotine, together with a range of psychological and physiological withdrawal symptoms, contribute to high relapse rates (2–4).

TUD is characterized by compulsive tobacco use and frequent relapse, even among individuals aware of its harmful consequences (5). Common withdrawal symptoms—including craving, irritability, anxiety, depressed mood, and sleep disturbances—may persist for weeks or months and undermine cessation attempts (6). Effective treatment strategies therefore need to address both neurobiological dependence and behavioral regulation (7). Although nicotine replacement therapy (NRT), delivered via patches, gums, or lozenges, is widely used to reduce withdrawal symptoms, its effectiveness is limited by adverse effects and relapse after treatment discontinuation (8, 9). These limitations highlight the need for adjunctive interventions targeting both the physical and psychological aspects of nicotine dependence (9).

Acupuncture, a key modality of traditional Chinese medicine, has been investigated as a complementary approach for addiction treatment (10). Previous studies suggest that acupuncture may alleviate nicotine craving and withdrawal-related symptoms, potentially through modulation of neurochemical pathways and autonomic nervous system activity (11). However, existing evidence remains inconsistent, partly due to heterogeneity in acupuncture protocols and study design (12).

The present study introduces HMA, an integrative protocol designed to address both physical and emotional symptoms associated with nicotine withdrawal. HMA integrates traditional meridian theory with neurofunctional acupuncture point selection to target craving, emotional dysregulation, and autonomic imbalance. This pragmatic randomized controlled trial aims to evaluate the effectiveness and safety of HMA in combination with NRT in individuals with TUD under real-world clinical conditions. The primary objective is to evaluate the effect of HMA plus NRT on nicotine craving reduction; secondary outcomes assess abstinence rates and psychological measures. HMA employs a multidomain acupuncture point strategy intended to influence central neural processes, stabilize emotional responses, and support physiological regulation. This integrative approach is designed to address multiple components of nicotine withdrawal that may not be fully targeted by pharmacotherapy alone. Although evidence for acupuncture in substance dependence remains mixed, particularly for auricular approaches, emerging studies suggest that body- and scalp-based protocols targeting prefrontal–limbic circuitry may be associated with reductions in craving and improvements in affective symptoms. This pragmatic trial is expected to contribute to the existing evidence base by evaluating a standardized, symptom-oriented acupuncture protocol in combination with NRT in a clinically relevant setting.

## Methods

2

### Study design and setting

2.1

This study is a pragmatic, randomized, single-center, parallel-group clinical trial designed to evaluate the effectiveness and safety of HMA as an adjunct to NRT in individuals with TUD.

The study has been approved by the Ethics Committee of the Affiliated Hospital of Yunnan University (approval number: KJR#20251111-R1-055) and registered with the International Traditional Medicine Clinical Trial Registry (ITMCTR2026000683). The protocol was developed in accordance with the SPIRIT 2013 guidelines and the Standards for Reporting Interventions in Controlled Trials of Acupuncture (STRICTA) recommendations (13–15). Written informed consent will be obtained from all participants prior to enrollment.

An overview of the trial flow is presented in Figure 1, and the schedule of enrollment, interventions, and assessments is shown in Table 1. This study is designed to assess the real-world effectiveness of HMA when used alongside standard nicotine replacement therapy in routine clinical practice.

**Figure 1 fig1:**
[figure not shown]
Flowchart of the pragmatic randomized controlled trial evaluating HMA combined with NRT. This diagram outlines the study design and procedural timeline, including screening, random allocation to two groups (HMA + NRT vs. NRT alone), the intervention schedule, assessment time points, and follow-up. The co-primary outcomes are: (1) change in nicotine craving intensity assessed by the visual analog scale (VAS) from baseline to week 6; and (2) 7-day point prevalence abstinence (PPA) at week 6 biochemically verified by exhaled carbon monoxide. Secondary outcomes include exhaled carbon monoxide (as a continuous measure), quality of life (SF-36), sleep quality (PSQI), depressive symptoms (BDI-II), and anxiety symptoms (BAI). Safety monitoring, including adverse event (AE) reporting and clinical evaluations, is conducted throughout the trial.

**Table 1 tab1:** Participant flow and study timeline.

Timepoint (week)	-1	0	2	4	6	10	24
Enrollment phase							
Screening	×						
Informed Consent		●					
Allocation		●					
Intervention phase							
HMA + NRT Group		●	●	●	●		
NRT-only Group (+ health education for attention control)		●	●	●	●		
Assessment phase							
VAS (Nicotine Craving) (Co-primary outcome)		●	●	●	●	●	●
PPA (7-day Point Prevalence Abstinence) (Co-primary outcome)					●		●
CO (Exhaled Carbon Monoxide)		●	●	●	●	●	●
SF-36 (Quality of Life)		●		●	●	●	●
PSQI (Sleep Quality)		●		●	●	●	●
BDI-II (Depression Symptoms)		●		●	●	●	●
BAI (Anxiety Symptoms)		●		●	●	●	●
Safety monitoring							
Adverse events		●	●	●	●	●	●

This table presents a detailed overview of the study schedule, including participant enrollment, administration of interventions (HMA plus NRT or NRT alone), assessment timepoints for outcome measures, and safety monitoring (adverse events). Black dots (●) indicate the scheduled activities at each timepoint. The co-primary outcomes are: (1) change in VAS from baseline to week 6; and (2) 7-day point prevalence abstinence (PPA) at week 6.

### Participants

2.2

#### Recruitment and screening

2.2.1

Participants will be recruited through posters and institutional bulletins at the Affiliated Hospital of Yunnan University. Individuals who express interest will undergo an initial screening conducted by trained study personnel to assess eligibility based on predefined inclusion and exclusion criteria. Baseline and post-randomization treatment expectancy will be measured using the CEQ. Between-group differences will be incorporated into statistical models if imbalances are detected (16). Baseline assessments will include nicotine dependence severity (FTND), prior quit attempts, use of e-cigarettes or other nicotine products, and concurrent behavioral support (17).

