The sample size was calculated based on the co-primary outcome of 7-day point prevalence abstinence (PPA) at week 6. Referring to recent systematic reviews of acupuncture smoking cessation trials (21, 22), a control group abstinence rate of approximately 15% was assumed, with an odds ratio (OR) of 1.9 for the HMA + NRT group. With a two-sided significance level of *α* = 0.05, 80% power, and a 1:1 allocation ratio, a total of 188 participants is required. Accounting for a 15% dropout rate, the final sample size is set at 220 participants (110 per group) (23). The VAS craving outcome, as the other co-primary endpoint, is also adequately powered based on the same sample size. Multiplicity control. Because two co-primary outcomes are designated, the overall type I error rate is controlled using the Hochberg procedure. Under this approach, each outcome is tested at the full *α* = 0.05 level; the family-wise error rate is preserved because the trial is considered positive only if both co-primary outcomes achieve statistical significance (*p* ≤ 0.05 each). This method offers greater power than Bonferroni correction while maintaining strong control of the family-wise error rate.

To monitor expectancy and attention effects, participants will complete the Credibility/Expectancy Questionnaire (CEQ) at baseline and post-randomization; these scores will be explored in sensitivity analyses (16).

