#### Control intervention (nicotine replacement therapy)

2.4.2

Both groups will receive the same NRT regimen. Participants in the control group will receive NRT alone for 6 weeks.

The NRT regimen consists of transdermal nicotine patches administered at a fixed dose of 21 mg/day for the first 4 weeks, followed by 14 mg/day for weeks 5–6 (31). No dose adjustment based on VAS scores will be performed to avoid confounding feedback between the intervention and NRT dosage. All NRT doses will be recorded as administered and included as a covariate in sensitivity analyses.

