Between-group differences in clinical contact and expectancy scores will be explored and adjusted for in sensitivity analyses to account for attention-related effects (16).

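### Section 2.2.1 would put expectancy scores, including those taken after allocation, into the models when an imbalance is seen, while the rest of the article keeps them in sensitivity analyses

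*Protocol article*

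**What the plan says.** The protocol article handles expectancy in four places.

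- Section 2.2.1 collects the CEQ at baseline and after randomisation, then states: "Between-group differences will be incorporated into statistical models if imbalances are detected". No criterion for imbalance is given, and neither the score nor the type of model is restricted.
- Section 2.3 says of the same two measurements that "these scores will be explored in sensitivity analyses".
- The end of section 2.10.1 says: "Between-group differences in clinical contact and expectancy scores will be explored and adjusted for in sensitivity analyses". The stated purpose is to account for attention-related effects.
- Section 3.1 again places the expectancy scores in sensitivity analyses and credits them with mitigating attention-related bias.

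Two other provisions bear on the point. In section 2.10.1 the craving model has group, time, their interaction and a random intercept, while the week-6 abstinence result is to be an odds ratio described as adjusted, with no covariates named. Section 2.4.2 says of nicotine replacement: "All NRT doses will be recorded as administered and included as a covariate in sensitivity analyses".

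**The concern.** Section 2.3 states that participants cannot be blinded. A CEQ score taken after they learn their arm may therefore differ between arms because of the allocation, and it may in turn affect craving, which is self-rated. The same section sets the aim as the incremental effectiveness of adding acupuncture to standard therapy in real-world care. That is a total effect, and any part that runs through expectancy belongs to it. Conditioning on post-allocation expectancy takes that part out. If something unmeasured influences both expectancy and outcome, conditioning also creates collider bias.

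The imbalance trigger makes this worse. The design may well produce an arm difference in post-allocation expectancy, so whether the reported estimate is the total effect or something smaller would depend on the data.

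The sensitivity analyses are affected in a lesser way. Section 3.1 relies on expectancy adjustment, and section 2.10.1 on expectancy and contact adjustment, to deal with attention effects in a trial without sham. If they cannot do so, an attenuated result may be misread as no specific effect, and an unchanged one as proof against bias.

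**Working it through.** **Plan's own figure.** The article gives no figure for this point. Its sample-size statement supplies only N = 220 (110 per arm). How that N was derived is a separate matter and is not used here.

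**Step 1: the passages side by side.**

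| Section | Variable | Where it enters | Condition |
|---|---|---|---|
| 2.2.1 | CEQ, baseline and post-randomisation | statistical models, unrestricted | if imbalance seen |
| 2.3 | same scores | sensitivity analyses | none |
| 2.10.1, end | expectancy and contact | sensitivity analyses | none |
| 3.1 | same scores | sensitivity analyses | none |
| 2.4.2 | NRT dose as administered | sensitivity analyses | none |

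Section 2.2.1 is the only one that leaves the model open and the only one with a trigger. Nothing in section 2.10.1 keeps its rule out of the unnamed covariates of the abstinence odds ratio.

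**Step 2: effect of following 2.2.1 with the post-allocation score.** All effect sizes are assumptions, since the article gives none. A continuous outcome was simulated in 220 participants, 4,000 runs per scenario:

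- expectancy = a × arm + noise (SD 1), with a = 0.2 to 0.8
- outcome = 0.2 × arm + 0.4 × expectancy + noise (SD 1)
- true total effect = 0.2 + 0.4a
- common-cause version: an unmeasured factor enters both equations with weight 0.5
- trigger: adjust if the arm difference in expectancy is significant at the 5% level

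The adjusted estimate can be checked by hand. Without a common cause it is (0.2 + 0.4a) − 0.4a = 0.20. With one, the within-arm slope of outcome on expectancy is 0.4 + 0.5 × 0.5 = 0.65, so the estimate is (0.2 + 0.4a) − 0.65a = 0.2 − 0.25a.

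| Shift a | True total | Unadjusted | Adjusted, no common cause | Triggered, no common cause | Adjusted, common cause | Triggered, common cause | Trigger fires (no common cause) |
|---|---|---|---|---|---|---|---|
| 0.2 | 0.28 | 0.28 | 0.20 | 0.24 | 0.15 | 0.21 | 32% |
| 0.3 | 0.32 | 0.32 | 0.20 | 0.23 | 0.13 | 0.17 | 60% |
| 0.5 | 0.40 | 0.40 | 0.20 | 0.21 | 0.07 | 0.08 | 96% |
| 0.8 | 0.52 | 0.52 | 0.20 | 0.20 | 0.00 | 0.00 | 100% |

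At modest shifts, chance decides which quantity is reported. With no true effect, no slope of outcome on expectancy, a common cause and a = 0.5 or 0.8, the adjusted test rejects in 13% or 24% of runs instead of 5%.

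With a = 0, which is how a pre-randomisation score behaves, the true effect is 0.20 and both the unadjusted and the triggered estimates average 0.20. The bias therefore belongs to the post-allocation score, not to baseline CEQ.

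**Step 3: contact time as a covariate.**

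- Acupuncture arm (section 2.4): 18 sessions × 30 min = 540 min.
- Control arm, extra education (section 2.4.4): 5–10 min per visit, so 4 × 5 = 20 min (visits to week 6, low end) up to 6 × 10 = 60 min (all visits, high end). Section 2.4.4 calls this matched to the acupuncture sessions, but its own minutes are not.
- Arm difference d = 540 − 60 = 480 to 540 − 20 = 520 min. Counselling is common to both arms and cancels.
- With 1:1 allocation, variance inflation = 1 + (d/2)² / SD², where SD is the within-arm SD (assumed).

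| SD (min) | Variance inflation | Standard error multiplied by |
|---|---|---|
| 30 | 65 to 76 | 8.1 to 8.7 |
| 60 | 17 to 20 | 4.1 to 4.4 |
| 90 | 8.1 to 9.3 | 2.8 to 3.1 |
| 120 | 5.0 to 5.7 | 2.2 to 2.4 |

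Example: SD 30, d = 480 gives 1 + (240/30)² = 65.

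**The case against.** The strongest reply is that the co-primary estimates are not adjusted for any of this. The craving model in section 2.10.1 names no CEQ, contact or NRT term. Sections 2.3, 2.4.2, 2.10.1 and 3.1 all say sensitivity analyses, and the sentence in 2.2.1 sits in a recruitment section and can be read in line with them. This largely stands. A reader might infer that the primary analyses as planned are biased; the article does not support that. It supports only that one sentence permits such adjustment and conflicts with the others. Leaving the covariates of the abstinence odds ratio to a fuller plan is not a fault in itself. It matters only because 2.2.1 supplies a rule that could fill the gap.

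A reader might also infer that an expectancy-adjusted model has no causal meaning. That goes too far. With no unmeasured common cause and no interaction it estimates a direct effect, and the simulation returns exactly the 0.20 that was built in. The fault is in presenting it as protection for the total effect.

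Finally, a reader might take the NRT dose to be caused by the arm. Section 2.4.2 fixes the same regimen for both arms, and nothing says that use will differ. Dose as administered reflects post-randomisation adherence, so dependence on arm is possible but not stated.

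**Conclusion.** The article gives two incompatible rules for one variable. The looser one, in section 2.2.1, is triggered by the data and includes a score that allocation can influence. It should be corrected, but it is a wording-level fault and does not show that the specified co-primary analyses are biased.

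If 2.2.1 were followed, a true effect of 0.28 to 0.52 SD would be reported on average as about 0.20 to 0.24 SD, or 0.00 to 0.21 SD with a common cause. These sizes rest on the assumed direct effect, slope, shift and 5% trigger, for a continuous outcome. The same argument applies to abstinence, but its size was not computed.

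The near-collinearity of contact with arm follows from the article's own minutes. Only the degree, a 5- to 76-fold variance inflation, depends on the assumed SD, and it affects sensitivity estimates alone. Neither expectancy nor contact adjustment can bear the weight that sections 2.10.1 and 3.1 place on them. The NRT covariate is a minor labelling point.

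**What to change.** - **Section 2.2.1:** replace the imbalance rule with a statement that baseline (pre-randomisation) CEQ is a prespecified covariate in a sensitivity model regardless of any observed difference, and that no post-randomisation variable enters either co-primary model. Bring 2.3 and 2.10.1 into line.
- **Section 2.10.1:** drop contact time as a covariate. Report post-randomisation CEQ and contact time by arm descriptively, or in an exploratory mediation analysis labelled as not estimating the total effect.
- **Section 2.4.2:** give any sensitivity model that uses NRT dose as administered the same label.
- **Section 3.1:** soften the claim that expectancy scores mitigate attention-related bias.

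The cost is wording only. Sample size, visits and data collection do not change. The contact-adjusted sensitivity model is lost and the expectancy-adjusted one is relabelled.

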#### Inclusion criteria

2.2.2

Participants meeting all of the following criteria will be eligible for inclusion:

(1) Aged 18–60 years;(2) Diagnosis of TUD according to the DSM-5 (18);(3) Smoking at least 10 cigarettes per day for at least 1 year;(4) Willingness to quit smoking and to initiate and adhere to nicotine replacement therapy as specified in the study protocol;(5) No acupuncture treatment within the previous 3 months;(6) Ability to provide written informed consent and comply with study procedures.

#### Exclusion criteria

2.2.3

Participants meeting any of the following criteria will be excluded:

(1) History of severe cardiovascular, hepatic, renal, or pulmonary disease;(2) Uncontrolled or severe comorbid conditions (e.g., decompensated liver cirrhosis, end-stage renal disease, unstable cardiovascular disease, active malignancy, or active tuberculosis);(3) Severe or unstable gastrointestinal disorders (e.g., active inflammatory bowel disease or recent gastrointestinal bleeding) or clinical malnutrition;(4) Severe or unstable psychiatric disorders (e.g., active psychosis, untreated major depressive disorder with severe symptoms, or bipolar disorder in a manic phase) or significant cognitive impairment affecting informed consent or protocol adherence;(5) Use of concurrent medications or therapies that may confound study outcomes;(6) Local skin infection, inflammation, scarring, or trauma at intended acupuncture sites;(7) Pregnancy or intention to conceive during the study period.

### Randomization, blinding and sample size

2.3

The use of a usual-care control group (NRT alone) rather than a sham acupuncture comparator reflects the pragmatic objective of this trial. The primary aim is to evaluate the incremental effectiveness of harmonizing mind acupuncture when added to standard smoking cessation therapy in real-world clinical settings.

Although sham acupuncture is commonly used in explanatory trials, its validity as a physiologically inert control remains debated.

Therefore, this study prioritizes clinical relevance and applicability by comparing HMA plus NRT with NRT alone, consistent with routine integrative practice.

Eligible participants will be randomly assigned in a 1:1 ratio to the intervention group (HMA plus NRT) or the control group (NRT alone) using a computer-generated block randomization scheme with a block size of four. The randomization sequence will be generated by an independent statistician using the REDCap platform (version 13.0; Vanderbilt University) and will be concealed from all study personnel involved in participant recruitment, intervention delivery, and outcome assessment (19).

Allocation concealment will be ensured using the sequentially numbered, opaque, sealed envelope (SNOSE) method (20). Envelopes will be opened sequentially by a designated study coordinator only after completion of baseline assessments.

Due to the nature of the acupuncture intervention, blinding of participants and acupuncturists is not feasible. However, outcome assessors, data managers, and statisticians will remain blinded to group allocation. Group assignments will be coded using anonymized labels (e.g., Group A and Group B) to minimize detection and analysis bias.

The sample size was calculated based on the co-primary outcome of 7-day point prevalence abstinence (PPA) at week 6. Referring to recent systematic reviews of acupuncture smoking cessation trials (21, 22), a control group abstinence rate of approximately 15% was assumed, with an odds ratio (OR) of 1.9 for the HMA + NRT group. With a two-sided significance level of *α* = 0.05, 80% power, and a 1:1 allocation ratio, a total of 188 participants is required. Accounting for a 15% dropout rate, the final sample size is set at 220 participants (110 per group) (23). The VAS craving outcome, as the other co-primary endpoint, is also adequately powered based on the same sample size. Multiplicity control. Because two co-primary outcomes are designated, the overall type I error rate is controlled using the Hochberg procedure. Under this approach, each outcome is tested at the full *α* = 0.05 level; the family-wise error rate is preserved because the trial is considered positive only if both co-primary outcomes achieve statistical significance (*p* ≤ 0.05 each). This method offers greater power than Bonferroni correction while maintaining strong control of the family-wise error rate.

To monitor expectancy and attention effects, participants will complete the Credibility/Expectancy Questionnaire (CEQ) at baseline and post-randomization; these scores will be explored in sensitivity analyses (16).

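### A single published block size of four, in an open-label single-centre trial with sequential envelopes, lets anyone who follows past assignments know one allocation in three in advance

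*Protocol article*

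**What the plan says.** All of the allocation rules are in section 2.3 of the protocol article (Randomization, blinding and sample size).

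- Assignment is 1:1, "using a computer-generated block randomization scheme with a block size of four". One size is given; varying sizes and stratification are not mentioned.
- An independent statistician generates the sequence with REDCap, and it "will be concealed from all study personnel involved in participant recruitment, intervention delivery, and outcome assessment".
- Concealment is by sequentially numbered, opaque, sealed envelopes. "Envelopes will be opened sequentially by a designated study coordinator only after completion of baseline assessments".
- Treatment is open on the delivery side: "blinding of participants and acupuncturists is not feasible". Assessors, data managers and statisticians are to stay blinded.

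The abstract and section 2.1 describe a single-centre trial, and section 2.3 plans 220 participants, 110 per arm. Section 2.2.1 gives screening to trained study personnel. It does not say whether the envelope-opening coordinator is one of them. Table 1 puts screening at week -1 and consent and allocation at week 0.

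**The concern.** A sealed envelope hides its own contents. It cannot hide what follows by subtraction from envelopes already opened. With two places per arm in every block of four, the rest of a block is fixed as soon as one arm has used its two places. The block size is printed in a public article, and past assignments are visible because one arm attends 18 acupuncture sessions over 6 weeks. The trial runs on what appears to be one local series of envelopes, so blocks can be counted off from the envelope numbers.

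At stake is who enters which arm. Opening the envelope after baseline protects the baseline measurements, but the decision to enrol, defer or exclude comes earlier. Some criteria need judgement: willingness to quit and to adhere to NRT (section 2.2.2), and concurrent medications or therapies that might confound outcomes (section 2.2.3). The interval between screening and allocation in Table 1 also leaves room to time an entry. If staff with foreknowledge influenced those decisions, the arms could differ at entry. Blinded assessment and carbon monoxide verification would not correct that, because they address measurement and not enrolment.

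**Working it through.** The protocol gives no predictability figure to reproduce, so this is a direct enumeration.

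**Inputs (section 2.3).** Block size 4; ratio 1:1, hence two places per arm per block; 220 participants, hence 220 / 4 = 55 complete blocks.

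**Observer assumed.** Knows the block size, all earlier assignments in order, and where each block starts. The last of these assumes one unstratified series of envelopes.

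**Certain allocations.** There are C(4,2) = 6 equally likely blocks. An allocation is certain when one arm's two places are already used.

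| Blocks | Places known in advance | Number certain |
|---|---|---|
| AABB, BBAA | 3rd and 4th | 2 |
| ABAB, ABBA, BAAB, BABA | 4th | 1 |

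- Mean per block: (2 × 2 + 4 × 1) / 6 = 1.333 of 4, or 33.3%.
- Over the trial: 55 × 1.333 = 73.3 of 220.
- Each block contributes 1 plus an extra 1 with probability 1/3, so the SD is √(55 × 1/3 × 2/3) = 3.5.
- Limits: at least 55 × 1 = 55 and at most 55 × 2 = 110. Counting only the last place in each block gives 55 / 220, one in four.

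**Best-guess rate.** The observer names the arm with more places left and tosses a coin on ties. The chance of being right is 1/2 at the first place, 2/3 at the second, 1/3 × 1 + 2/3 × 1/2 = 2/3 at the third, and 1 at the fourth. The mean is (1/2 + 2/3 + 2/3 + 1) / 4 = 70.8%.

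**Alternatives.** Longer fixed blocks were enumerated in the same way. Randomly varying blocks were simulated (220 allocations, 300 runs per scheme) for an observer who knows the set of sizes but not the size of each block. The size sets are assumptions of this review. Run on the fixed block of four, the simulation returned 33.4% certain and 70.8% best guess, in agreement with the enumeration.

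| Scheme | Certain | Best guess |
|---|---|---|
| Fixed 4 (protocol) | 33.3% | 70.8% |
| Fixed 6 | 25.0% | 68.3% |
| Fixed 8 | 20.0% | 66.6% |
| Random 4, 6 | 5.5% | 69.3% |
| Random 2, 4, 6 | 4.3% | 70.1% |
| Random 4, 6, 8 | 2.0% | 68.0% |

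Out of 220, 2.0% is about 4 participants and 5.5% about 12. Varying the sizes removes certainty but barely changes the average quality of a guess.

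**The case against.** The strongest reply is that the one-in-three figure is a ceiling for a perfectly informed observer, and that the protocol keeps such an observer away from enrolment. An independent statistician makes the list, recruiters do not see it, a coordinator opens the envelopes, and other personnel screen. Staff who merely see people attending acupuncture would still need the order of enrolment and the interleaved control participants to rebuild a block. This largely stands as a limit on the claim. It does not dispose of it: the coordinator does hold the earlier assignments in order, and the article does not separate that role from screening or rule out information passing between them.

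A reader might infer more than the documents support, in four ways.

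- *That a third of participants will be enrolled with foreknowledge, or that concealment has failed.* The 73 are allocations that can be deduced, not enrolments known to be influenced.
- *That the plan costs 21 points of predictability, 71% against 50%.* The 50% belongs to randomization without blocks. Against the varying blocks suggested here the difference is about 3 points.
- *That motivation to quit is the route of bias for both co-primary outcomes.* This is plausible, but the article does not establish it, and its requirement of willingness to quit narrows the range of motivation.
- *That any resulting bias would be beyond repair.* Nicotine dependence, prior quit attempts and expectancy are recorded (section 2.2.1), so bias acting through them could be examined and partly adjusted for. Bias through unmeasured factors could not.

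**Conclusion.** The point holds as an avoidable weakness in allocation concealment. The stated block rule makes 33% of allocations, about 73 of 220, deducible with certainty by a person who knows past assignments and block starts, and the stated concealment steps do not prevent that deduction. The arithmetic is exact given a 1:1 ratio, a fixed block of four and a single series of envelopes; the last is inferred from the absence of any mention of stratification.

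Whether the deduction could affect enrolment depends on whether the envelope-opener, or someone informed by that person, has a say in who enters and when. The article does not settle this. It is therefore a stated rule worth changing and does not by itself invalidate the trial.

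**What to change.** Before the first participant, or for all remaining allocations if enrolment has begun:

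1. Have the independent statistician regenerate the list with randomly varying block sizes, for example 4, 6 and 8.
2. Hold the sizes in a restricted document that site staff cannot see, and do not publish them until recruitment ends.
3. State in section 2.3 that the person who opens envelopes takes no part in screening or enrolment decisions and does not pass on past assignments.

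Steps 1 and 2 bring the certain share down to about 2% (about 5.5% with sizes 4 and 6). Step 3 is needed as well, because the best-guess rate stays near 68%.

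The cost is a new list from a system already used to generate the present one, a revised paragraph, and a possible final imbalance of up to four participants if the last block of eight is cut off halfway. On-demand release of each assignment from REDCap after baseline is an optional further step if the site can support it. The article mentions REDCap only for generating the sequence, so this would be an operational change whose cost it does not show.
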